## Discussion

Before progressing to follow-up studies of IRE in renal masses it is vital to perform tissue specific testing of IRE ablation efficacy and safety. This trial will investigate IRE ablation efficacy by comparing 3D histopathological examination of a (partially) resolved IRE lesion, through radical nephrectomy with 1) examination of 3D imaging using MRI and CEUS and 2) 3D prediction of ablation volume as given by the manufacturer. IRE ablation volume and shape is influenced by many variables such as needle number, needle configuration, and device/pulse settings. With only 10 IRE ablations it is not within in the scope of this study to experiment with a wide variety of IRE settings. We aim to test 2 needle electrode configurations, while keeping the device settings constant. In clinical practice contrast enhanced CT scanning is most widely used modality for follow-up after renal mass treatment. In this study however it was decided not to investigate CT imaging in order to limit the cumulative radiation exposure. Study participants are already receiving an estimated 32 mSv of ionizing radiation due to the CT guided IRE procedure. Adding CT follow-up to the research protocol would result in 2–3 additional 4 phase CT scans, besides any CT scans that are necessary after the final treatment. Another limitation of this study is the follow-up period, which is limited at 4 weeks. Animal trials have shown renal IRE lesions to be partially resolved at 3–4 weeks [20-22]. Preferably radical nephrectomy would be postponed longer than 4 weeks, giving the IRE lesion more time to mature, allowing for better analysis of intermediate ablation results. However, further prolonging the final treatment is unethical at this early phase of the research. A final limitation is the tumour size. Patients who are candidate for radical nephrectomy, except for patients with ERDS, will have tumours larger than 4 cm. Ablative therapies are indicated for tumours ≤ 4 cm, which means that we not testing renal IRE in the intended population. The choice for radical nephrectomy was made out of the concern that IRE ablation might complicate a subsequent partial nephrectomy leading to impaired surgical outcome. In our opinion this trial will provide essential knowledge on IRE of renal masses, guiding future research of this promising ablative technique.

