Animal trials have assessed the use of MRI and CT imaging for the intermediate follow-up of IRE lesions. Contrast enhanced CT imaging directly after IRE ablation of porcine kidney showed a hypodense non-enhancing lesion, persisting at 1 week post IRE. At 3 weeks, 4 out of 6 IRE lesions had disappeared completely [22]. Thomson et al. performed in human IRE in 10 renal tumours with subsequent follow-up by CT imaging. At 3 months post IRE incomplete ablation was diagnosed in 2 patients on the basis of CT-imaging. However, the authors provide little information on the imaging characteristics of the residual lesion. MRI directly after IRE of porcine kidney showed a localized oedema at the region of IRE ablation. At 7 days after IRE a hypo-intense necrosis-like lesion in the renal parenchyma at the region of IRE was visualised. Finally, at 28 days a sharply delineated, non-intense, scar-like lesion with cortical shrinkage and without contrast enhancement was visualised [20]. These results provide an insight in the use of imaging for the follow-up of renal IRE. However, a study where follow-up imaging, specifically assessment of ablation volume and residual enhancing tumour, is correlated to histopathology of the resected specimen has not yet been performed.

Procedural safety of renal IRE in humans has been tested and confirmed [15]. The electric pulses administered during IRE have the potential of causing cardiac arrhythmias; by synchronising the IRE pulses with the ECG this complication can be avoided [23]. In a study by Pech et al., ablated tumours were resected directly after IRE and they observed swelling of cells but no actual cell death. However, histological staining to assess cell viability was not performed [15].

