Before progressing to a long-term IRE follow-up study it is vital to have pathological confirmation of the efficacy of the technique. Furthermore, follow-up of IRE ablation requires an accurate imaging modality. This trial will investigate IRE ablation efficacy by correlating 3D histopathology of a resected IRE lesion with: 1) 3D reconstructed imaging using MRI and contrast enhance ultrasound (CEUS), and 2) the 3D predicted ablation volume as provided by the manufacturer. The objectives of the study are assessing the safety and efficacy of IRE of renal masses (primary objectives), and assessing the efficacy of MRI and CEUS for the initial evaluation and short-term (4 weeks) follow-up of IRE lesions (secondary objectives). This study conforms to the recommendations of the IDEAL Collaboration and can be categorised as a phase 2A development trial [24].

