### Study design

This is a prospective, human, in-vivo study among 10 patients presenting with a solid renal mass, and candidates for radical nephrectomy (RN). A study flowchart is provided in Figure 1. Prior to the IRE procedure baseline MRI and CEUS imaging will be acquired. Subsequently the patients will undergo IRE ablation of their renal mass. Follow-up at one and four weeks post IRE will be performed using MRI and CEUS imaging. At these time points procedure and device related adverse events (AE) will be registered using the Common Terminology Criteria for Adverse Events (CTCAE) version 4.0 guideline. Four weeks after IRE the patients will undergo radical nephrectomy after which pathological examination will be performed to evaluate IRE ablation success. Core biopsies are harvested before IRE ablation in order to assure tumour differentiation in case of complete ablation. Correlation between pathology and imaging will reveal the efficacy of MRI and CEUS for the assessment of IRE lesions.

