**Study design flowchart.**

### Study objectives

Primary objectives:To determine the efficacy of IRE ablation of renal masses, measured by pathological examination of the targeted tumour.To determine the safety of IRE ablation of renal masses, by evaluating device and procedural adverse events using CTCAE v4.0.

Secondary objectives:To evaluate the efficacy of MRI in the imaging of ablation success, the extent of the ablation zone, one and four weeks post IRE ablation.To evaluate the efficacy of CEUS in the imaging of ablation success, the extent of the ablation zone, one and four weeks post IRE ablation.

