##### Radical nephrectomy (standard treatment)

Radical nephrectomy will be performed four weeks after renal IRE ablation, either open or laparoscopic depending on patient specific factors such as co-morbidities and tumour characteristics. It will be performed according to department protocol by two experienced urologic surgeons.

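### Predicted ablation volume, and possibly one-week imaging, is judged against four-week histology of a partly resolved lesion, and the stated summaries cannot separate resolution from error

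*Protocol article*

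**What the plan says.** All references are to the Protocol article.

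- **One histology time point.** Radical nephrectomy (standard treatment): "Radical nephrectomy will be performed four weeks after renal IRE ablation".
- **Comparison with the prediction.** Background lists among the comparators "the 3D predicted ablation volume as provided by the manufacturer". Under Analysis, that volume is built by stacking the console's predicted cross sections along the exposed electrode tip. The Discussion repeats the comparison and describes the resected specimen as that of a lesion which may already be partly resolved: "comparing 3D histopathological examination of a (partially) resolved IRE lesion".
- **Reference for imaging.** Study design: "Correlation between pathology and imaging will reveal the efficacy of MRI and CEUS for the assessment of IRE lesions". No other reference is named. Study objectives ask for the efficacy of MRI and of CEUS in showing "the extent of the ablation zone, one and four weeks post IRE ablation".
- **Lesion course.** Discussion: "Animal trials have shown renal IRE lesions to be partially resolved at 3–4 weeks". Background, on porcine CT: "At 3 weeks, 4 out of 6 IRE lesions had disappeared completely", after the lesions had still been present at one week. On porcine MRI, a necrosis-like lesion at 7 days had become a scar-like one with cortical shrinkage at 28 days.
- **Status of the histology volume.** Analysis treats the histological reconstruction as giving the exact volume and shape of the lesion.
- **Summary.** Sample size limits the results to averages and standard deviations of the volumetric data.

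**The concern.** A volume comparison measures error only if both volumes describe the same lesion at the same time. The console predicts what is ablated during pulsing, while the specimen shows what is left four weeks later. Any resolution in between enters the histology/predicted ratio exactly as over-prediction would. Resolution could also hide an under-prediction, because the two act in opposite directions.

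The same holds for one-week imaging if its volumes are set against the specimen. An accurate image of a lesion that then shrinks would look like an overestimate.

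At stake is what the trial can say about the manufacturer's prediction and about one-week imaging of lesion extent. The Discussion treats four weeks only as a short follow-up and would have preferred longer. It does not say that resolution affects the volume comparisons.

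**Working it through.** The plan gives no figure for shrinkage, so there is none to reproduce. What can be checked is whether the planned quantities identify the error of interest, and how large the ambiguity could be.

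**Notation**
- s = fraction of the ablated volume resolved by week 4; w = fraction resolved by week 1. Neither is in the document; both are assumptions.
- p = predicted volume divided by the volume truly ablated at pulsing (p = 1 is a perfect prediction).
- Histology is taken as error-free at week 4.

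**1. Prediction against histology**

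Histology/predicted = (1 − s)/p: one observed ratio, two unknowns.

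- With p = 1, the ratio is 1 − s and the apparent over-prediction is s/(1 − s):

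| s (assumed) | histology/predicted | apparent over-prediction |
|---|---|---|
| 10% | 0.90 | 0.10/0.90 = 11% |
| 20% | 0.80 | 0.20/0.80 = 25% |
| 30% | 0.70 | 0.30/0.70 = 43% |
| 50% | 0.50 | 0.50/0.50 = 100% |

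- A ratio of 0.70 arises from p = 1 with s = 30%, and equally from s = 0 with p = 1/0.70 = 1.43.
- A ratio of 1.00 arises from p = 1 with s = 0, and equally from p = 0.70 with s = 30%, which is an under-prediction masked by resolution.

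The mean and standard deviation of such ratios, or of the two volumes, do not break the tie.

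**2. One-week imaging against histology, if so paired**

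For perfect one-week imaging, the apparent overestimation is (1 − w)/(1 − s) − 1:

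| | s = 20% | s = 30% | s = 50% |
|---|---|---|---|
| w = 0 | 25% | 43% | 100% |
| w = 10% | 12.5% | 29% | 80% |
| w = 20% | 0% | 14% | 60% |

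It is zero only when w = s, that is, when nothing resolves between weeks 1 and 4.

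**3. Four-week imaging against histology**

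Both describe the lesion at week 4, so the expression becomes (1 − s)/(1 − s) − 1 = 0. There is no timing error.

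**4. What the planned scans can add**

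With accurate MRI, the week-4/week-1 volume ratio is (1 − s)/(1 − w). A proportional MRI error that is the same at both visits cancels. Example: s = 30%, w = 10% gives 0.70/0.90 = 0.78, against a histology/predicted ratio of 0.70 under perfect prediction. The MRI ratio therefore shows most of the resolution but misses what happened before week 1.

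**5. The animal figure**

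4/6 = 67%, exact 95% confidence interval 22% to 96%. This is the share of porcine lesions no longer visible on CT at three weeks. It is not a volume loss and cannot be used as s.

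**The case against.** The strongest case against the point has four parts.

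- **The week-1 pairing is not written down.** No sentence sets one-week volumes against the specimen, and a condensed article may leave the matching of scans to the full protocol. This stands in part. The pairing is read from Study design (pathology as the reference) and Study objectives (one and four weeks) taken together, so the week-1 part is conditional. The comparison of prediction with histology is stated outright and does not depend on this reading.
- **The authors know of the resolution and plan only description.** True. A reader might infer that a correct prediction will be declared an over-prediction. The document does not support that: it sets no agreement threshold or rule, and it plans MRI at both one and four weeks. What remains is that the article does not use those scans to separate resolution from error.
- **The evidence is from animals.** True. A reader might take the lesion to be at full size at one week, or read 4 of 6 as two-thirds of the volume lost. Background says only that the CT lesion persisted at one week, and its figure concerns visibility in porcine kidney. The size of the effect in human tumours is unknown.
- **Week-1 MRI is a poor substitute reference.** It is not time zero, and MRI is itself under evaluation. This stands, so it should accompany histology and not displace it.

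**Conclusion.** The point holds for volume and extent. Under the stated summaries, lesion resolution cannot be told apart from error in the predicted volume. Nor can it be told apart from one-week imaging volume error, if those images are compared with the specimen. If 10–50% of the volume has resolved by week 4 (an assumption, not a figure from the document), a perfect prediction gives a histology/predicted ratio of 0.90–0.50, an apparent over-prediction of 11–100%. The mechanism is certain once resolution occurs; its size is not known.

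The limits matter. Week-4 MRI and CEUS against week-4 histology are unaffected, as is the pathological assessment of viable cells, so the primary efficacy objective is not undermined on this ground. A reader might also infer that one-week imaging has no valid reference at all. That goes too far: Analysis also has imaging read for residual tumour and skip lesions, and shrinkage of the dead zone is not shown to invalidate viable tissue at week 4 as a reference for those readings.

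**What to change.** 1. Use week-4 histology as the volumetric reference for the week-4 MRI and CEUS only. Report week-1 volume and extent as a description of lesion evolution, not as accuracy validated by pathology.
2. Keep the comparison of predicted volume with histology. Beside it, report predicted volume against week-1 MRI volume and each patient's week-4/week-1 MRI volume ratio. State that a histology/predicted ratio below 1 may reflect resolution, and that a ratio near 1 does not exclude under-prediction.

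**Cost.** Slightly more analysis of scans already planned, some rewording, and a more modest conclusion about week-1 imaging. Week-1 MRI is neither time zero nor a validated reference, so the added comparisons narrow the ambiguity without removing it. No new scan and no change to the timing of surgery is needed.

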## Abbreviations

AE: Adverse event
CCMO: Central Committee on Research Involving Human Subjects
CEUS: Contrast enhanced ultrasound
CTCAE: Common terminology criteria for adverse events
DSMB: Data safety monitoring board
EAU: European association of urology
ESRD: End stage renal disease
GFR: Glomerular filtration rate
ICD: Implantable cardioverter-defibrilator
IRE: Irreversible electroporation
IRB: Institutional Review Board
PN: Partial nephrectomy
RFA: Radio frequency ablation
RE: Reversible electroporation
RN: Radical nephrectomy
SRM: Small renal mass
NVU: Dutch Association of Urologists
VAS: Visual analogue scale
